##### Additional consent provisions for collection and use of participant data and biological specimens {26b}

Participants are informed that with signing the informed consent, they give permission for the research team to share relevant data whit regulatory authorities. On the consent form, the participant will be asked if they give permission to store the data for follow-up studies. Participants will also be asked for permission to contact them for future studies. This trial does not involve collecting biological specimens.

### Interventions

#### Explanation for the choice of comparators {6b}

We decided to compare HFNC to a control group with LFNC during deep sedation in patients with atrial fibrillation undergoing radiofrequency catheter ablation. LFNC is standard care during deep sedation [14]. It is expected that HFNC is superior to LFNC during deep sedation.

#### Intervention description {11a}

All randomised patients will receive standard care with regard to medications used for sedation and physiological monitoring or other interventions to support respiratory function that are considered necessary to be initiated during the procedure by the clinicians. Standard care is consistent with the ESA guideline on Procedural Sedation and Analgesia in Adults [14].

Deep sedation is defined as “A drug-induced depression of consciousness during which patients cannot be easily aroused but respond purposefully following repeated or painful stimulation”. Patients may require assistance in maintaining a patent airway, and spontaneous ventilation may be inadequate.

The physician assistant (PA) anaesthesiology or nurse anaesthetist (NA) administers a combination of analgesics and sedatives to target the level of deep sedation. There will be no restrictions of any dose ranges of the different medications used by the PA/NA. The actual doses of medication used will be registered. The PA/NA will record the doses of sedative medications used during procedures.

Oxygen therapy is administrated as indicated by randomisation. The device used for oxygen supplementation will be different.

For HFNC supplemental oxygen will be given with the Optiflow® device (Fisher and Paykel Healthcare, Auckland, New Zealand). The Optiflow® device has a heated breathing tube and chamber, and a nasal cannula will be used. The gas temperature will commence at high settings (37 °C) and titrated downwards if the patient complains of irritation. The gas flow rate will be started at 10 l/min prior to sedation. The gas flow rate of 10 l/min is usually well tolerated by awake patients. The gas flow will be increased after sedation has been administrated to 50 l/min. The gas flow can be titrated according to patients’ requirements. The flow rate is accommodated according to SpO_2_. The FiO_2_ will be set at 40%.

For LFNC, supplemental oxygen will be given with Microstream® Smart CapnoLine® O_2_. Oxygen supplementation is recommended to start at 5 l/min. The flow rate is accommodated according to SpO_2_. The clinician responsible for the sedation will in case of an upper airway obstruction combine the Microstream® Smart CapnoLine® O_2_ with a nasal or oral airway. The use of a nasal or oral Guedel airway is preferred above multiple airway repositioning to protect the clinician against unnecessary exposure to X-rays.

The cardiologic treatment RFCA for atrial fibrillation in combination with the required deep sedation often causes cardiac hemodynamic fluctuations due changes in heart rate. A low dose norepinephrine is used to prevent the occurrence of hypotension. The dose of norepinephrine is titrated to prevent hypotension due to arrhythmias. Temporary pacing is also permitted, due to the nature of the procedure. RFCA and deep sedation are part of the usual medical treatment.

Participants will receive oxygen via a nasal cannula.

There will be no invasive procedures performed. There will be no extra diagnostic procedures performed.

#### Criteria for discontinuing or modifying allocated interventions {11b}

Participants of the study will receive the best medical care.

Protocol deviation is possible in specific cases:Cross over from LFNC to HFNC in case of ongoing desaturation. Defined as a saturation < 90% > 180 s and is not improving after airway repositioning, tactile stimulation, increasing the supplemental oxygen or the use of an oral or nasal Guedel airwayCross over from HFNC to LFNC in combination with an oral or nasal airway in case of an airway obstruction caused by an upper airway collapse. Also cross over from HFNC to nasal low-flow oxygen if the participant is unable to tolerate the high-flow nasal cannula secondary to discomfort

#### Strategies to improve adherence to interventions {11c}

To improve adherence to the study protocol, the physician assistants (PA) anaesthesiology and nurse anaesthetist (NA) are trained and instructed on the study protocol, use of Optiflow and Sentec Vsign. Data from during sedation will be obtained from the on-line automatic patient data management system, PDMS.

#### Relevant concomitant care permitted or prohibited during the trial {11d}

Participating in this study will not require alternation to usual care pathways (including use of any medication).

#### Provisions for post-trial care {30}

The sponsor has an insurance which is in accordance with the legal requirements in the Netherlands (Article 7 WMO). This insurance provides cover for damage to research subjects through injury or death caused by the study.

### Outcomes {12}

#### Primary outcome

Primary outcome is the lowest SpO_2_. During PSA continuous SpO_2_ measurements will be recorded using SenTec Digital Monitoring with Vsign 2 sensor. Percentage haemoglobin saturated with oxygen will be measured continuously during the procedures as part of routine clinical practice through the anaesthetic monitoring. SpO_2_ monitoring will be measured by the sensor that is placed on the earlobe and recorded continuously.

Timeframe: The time from the first administration of sedative medication to stopping of the sedative medication (= the end of the procedure).

Measure method: Continuous SpO_2_ measurements will be recorded using SenTec Digital Monitoring with Vsign 2 sensor. SpO_2_ will be measured by the Vsign sensor that is placed on the earlobe and will be recorded continuously.

#### Secondary outcomes

The duration of the lowest SpO_2_

Timeframe: The time from the first administration of sedative medication to stopping of the sedative medication (= the end of the procedure)

Measure method: Duration of the lowest measured SpO_2_ in secondsCross over from oxygen therapy

Timeframe: The time from the first administration of sedative medication to stopping of the sedative medication (= the end of the procedure)

Measure method: cross over yes/noTo measure the incidence of hypoxemia and desaturation (SpO_2_ under 90% for > 60 s).

Timeframe: The time from the first administration of sedative medication to stopping of the sedative medication (= the end of the procedure)

Measure method: Incidence SpO_2_ under 90% for > 60 sThe area under the curve of oxygen desaturation (SpO_2_ under 90% for > 60 s).

This is an assembled measure comprising as the difference between threshold of 90% and actual oxygen saturation (SpO_2_) summed every second the duration of oxygen desaturation was longer than 60 seconds

Timeframe: The time from the first administration of sedative medication to stopping of the sedative medication (= the end of the procedure)

Measure method: Difference between SpO_2_ 90% (threshold) for > 60 s and the actual oxygen saturation summed every second during which the oxygen saturation was below thresholdThe incidence of adverse sedation events when oxygen supplementation through HFNC as compared to LFNC in patients with atrial fibrillation undergoing RFCA and deep sedation. The comprehensive research Tool for Tracking and Reporting Outcomes Of Procedural Sedation (TROOPS) is used to register adverse events [25]Completion of the tool requires identification and description of the adverse event, the intervention, the outcome and the overall severity of the incident. The PA/NA will be asked to complete this tool at the end of the procedureThe incidence of adverse effects of delivering high-flow nasal oxygen will be assessed. These adverse effects include pressure injury to the skin caused by the device and nose bleeding due to damage to the mucosal surface. The PA/NA will check the skin integrity around the nasal region at the end of the procedure. The observations will be documented in a case report form provided by the research assistantThe patient experience with the sedationIowa Satisfaction with Anaesthesia Scale (ISAS) is a validated questionnaire that is used to measure patient experience with the sedation during a procedure [3, 4].Timeframe: Before discharge from hospital (day of treatment + 1)The Mean TcCO_2_Timeframe: The time from the first administration of sedative medication to stopping of the sedative medication (= the end of the procedure)

Measure method: TcCO_2_ will be continuously measured during the whole procedure using SenTec Digital Monitoring with Vsign 2 sensor. TcCO_2_ monitoring provides continuous, accurate (mean bias − 0.1 mmHg) and precise (95 limits of agreements within 6 mmHg) estimates of arterial CO_2_ when the sensor is placed on the earlobeThe Peak TcCO_2_

Timeframe: The time from the first administration of sedative medication to stopping of the sedative medication (= the end of the procedure)

Measure method: TcCO_2_ will be continuously measured and recordedPatients rating of comfort of oxygen deliveryA 5-point Likert scale will be used to rate the patients comfort of oxygen delivery [18, 20]. Participants will be asked to rate their perceived overall comfort with the oxygen delivery device. A 5-point Likert scale is used with ratings of “very uncomfortable”, “uncomfortable”, “neutral”, “comfortable” and “very comfortable”.

Timeframe: Before discharge from hospital (day of treatment + 1)Rating of the physician assistant/nurse anaesthetist of difficulty maintaining oxygenation statusA 5-point Likert scale will be used to rate the PA/NA difficulty maintaining oxygenation status [3, 4]. The AC will be asked to rate their perceived level of difficulty using a 5-point Likert scale with ratings of “very difficult”, “difficult”, “neutral”, “easy”, “very easy”. If rated “very difficult” or “difficult” the AC specify their answer.

Timeframe: As soon as possible after the end of the procedure

Measure method: PA/NA rating of difficulty maintaining oxygenation status during the procedure using a 5-point Likert scaleRating of the physician assistant/nurse anaesthetist of user-friendliness of the oxygen delivery device.A 5-point Likert scale will be used to rate the PA/NA of user-friendliness of the oxygen delivery device [3, 4]. The AC will rate their perceived level of difficulty of maintaining oxygenation using a 5-point Likert scale with ratings of “very difficult”, “difficult”, “neutral”, “easy” and “very easy”. If rated “very difficult” or “difficult”, the physician assistant specifies their answer.

Timeframe: As soon as possible after the end of the procedure

Measure method: PA/NA rating of user-friendliness of the oxygen delivery device during the procedure using a 5-point Likert scaleRating the satisfaction of cardiologists with catheter stabilisation in relation to sedationA 5-point Likert scale will be used to rate the satisfaction of cardiologists with catheter stabilisation in relation to sedation will be rated with a 5-point Likert scale [3, 4]. The cardiologists will rate their perceived level of satisfaction with sedation using a 5-point Likert scale with rating of “very unsatisfied”, “unsatisfied”, “neutral”, “satisfied” and “very satisfied”. If rated “unsatisfied” or “very unsatisfied” the cardiologists specify their answer.

Timeframe: As soon as possible after the end of the procedure

Measure method: Satisfaction of cardiologists with sedation using a 5-point Likert scale

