**Methods:**

A single-centre, randomised controlled trial with HFNC as the intervention and LFNC as the control group. A total of 94 adult patients per group undergoing elective radiofrequency atrial fibrillation catheter ablation under deep sedation. will be included. The primary outcome is the lowest oxygen saturation (SpO_2_). Secondary outcomes are as follows: the duration of lowest SpO_2_, cross over from oxygen therapy in both directions, incidence of SpO_2_ below 90% > 60 seconds, adverse sedation events, adverse effects of HFNC, mean CO_2_, peak CO_2_ and patients experience with oxygen therapy. The study will take place during the 2-day admission period for RFCA. Patients can fill out their questionnaires in the first week after treatment.

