### Objectives {7}

The aim of this study is to test the hypothesis that oxygen supplementation via HFNC as compared to LFNC can prevent hypoxemia and desaturation in patients with atrial fibrillation undergoing RFCA and prolonged deep sedation of 3 h and more.

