##### Secondary outcomes

Cross over of therapy is a binary categorical variable. We will compare the difference in cross-over between groups using Pearson’s chi-squared test. The analysis of the incidence of hypoxemia is performed either with logistic or Poisson regression depending on the distribution. All continuous variables like area under the curve SpO_2_, ISAS score, mean TcCO_2_ and peak TcCO_2_ will be presented as group mean and SD. Univariable analysis using the independent-samples *t*-test will be performed. Further analysis will be done using multiple linear regression. Covariates will be specified as age, gender, BMI, ASA-classification, duration of RFCA procedure, hypotension and BIS. The occurrence of adverse events will be presented as count and percentage per group. Analysis will be performed using a logistic regression model. Likert type questions will be reported as percentage of patients that scored each of the options, stratified by group. The median for central tendency and frequencies for variability are calculated for analysing these descriptive statistics. The response on the Likert type questions will be analysed separately for each question using the Mann-Whitney *U* test.

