## Discussion

Procedural sedation and analgesia has become a common practice given the increasing demand to relieve anxiety, discomfort and pain during invasive diagnostic and therapeutic procedures. In 2018, the Department of Anaesthesiology at MUMC+ performed 2040 PSA procedures. The majority (*n* = 888) of PSA procedures were performed during RFCA and cardiac electrophysiology testing. Our experience is that as the procedure and PSA time increases saturation more often shows a gradual decrease and desaturations occur more frequent. The aim is to prevent patients for desaturations and hypoxemia. BMI as selection criteria was therefore decreased to 32 kg m^−2^ instead of 35 kg m^−2^. And the PSA (and procedure) time is limited to a maximum of 4 h.

To our knowledge, this is the first study to investigate the effects of HFNC during prolonged deep sedation in patients undergoing RFCA. HFNC is increasingly used as a technique for oxygen delivery in procedural sedation and analgesia The effect of HFNC vs LFNC during sedation has been investigated in several small studies. No difference in primary outcomes of oxygen desaturation was reported. The explanation could be the small sample-sizes and the level of sedation. The intervention could have a positive effect in this study because deep sedation is performed in supine position for a prolonged time up to 4 h.

The sample size in this prospective study was calculated and adjusted using a similar study which compared HFNC vs LFNC in a different population [26]. In this study, participants underwent dental surgery. However, the duration of sedation and treatment were shorter (< 75 min), which will affect primary outcome [26]. Therefore, we decided to perform a sample size control.

The secondary outcomes include ratings of experiences of participants and staff using 5 point Likert scales. Validated questionnaires were preferred, but unfortunately these are not available.

To ensure that all colleagues work according to the study protocol and follow GCP guidelines, education and training is provided. The AC are trained to obtain informed consent. The AC are instructed and trained in the use of the Optiflow and Vsign. They are also trained to provide PSA according to this study protocol during sedation. The group of PAs and AC exists of 7 colleagues.

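### The secondary outcome 'duration of the lowest SpO2' times each patient's own minimum, so its seconds are not comparable between patients and can run against the hypothesised benefit

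*Protocol article*

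**What the plan says.** The Abstract opens its list of secondary outcomes with this item: "Secondary outcomes are as follows: the duration of lowest SpO_2_, cross over from oxygen therapy in both directions". Under Outcomes {12}, Secondary outcomes, the measurement is "Measure method: Duration of the lowest measured SpO_2_ in" seconds, and the window is "The time from the first administration of sedative medication to stopping of the sedative medication (= the end of the procedure"). No saturation threshold, minimum depth, episode boundary or direction of benefit is given, and no rule for a patient who never desaturates.

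Two neighbouring secondary outcomes do use a fixed level. One records whether saturation stays under 90% for more than 60 s; the other sums the shortfall below 90% second by second over such episodes. The primary outcome is the minimum itself: "Primary outcome is the lowest SpO_2".

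Statistical methods {20a}, Secondary outcomes, does not name this item. Its general rule for continuous variables is group mean and SD, followed by: "Univariable analysis using the independent-samples *t*-test will be performed. Further analysis will be done using multiple linear regression".

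**The concern.** The level being timed is set by the patient's own trace. A shallow minimum close to the baseline is touched often and held for long; a deep nadir is usually touched briefly. More seconds can therefore go with better oxygenation, while the name of the outcome suggests the opposite.

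The stated hypothesis is that high flow "can prevent hypoxemia and desaturation in patients with atrial fibrillation undergoing RFCA". If it does so through fewer or shallower dips, the high-flow arm may show the longer duration. Under the general rule for continuous variables, that could produce a nominally significant secondary result that appears to contradict the primary one but only reflects how the outcome is defined.

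**Working it through.** The plan gives no figure for this outcome, so there is none to reproduce. The check applies the definition to traces.

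**Window.** Objectives {7} speaks of "prolonged deep sedation of 3 h and more", so 3 × 3,600 = 10,800 s. The Discussion says "the PSA (and procedure) time is limited to a maximum of 4 h", so 4 × 3,600 = 14,400 s.

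**Constructed traces** (one reading per second, 3 h, baseline 98%). Score = number of seconds at the trace minimum. The area counts whole episodes below 90% lasting more than 60 s.

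| Trace | Minimum | Score (s) | Seconds below 90% | Area below 90% (%·s) |
|---|---|---|---|---|
| Steady | 98 | 10,800 | 0 | 0 |
| One 10-s dip to 80% | 80 | 10 | 10 | 0 |
| One 300-s episode at 85% | 85 | 300 | 300 | 300 × 5 = 1,500 |
| Same episode, one of its seconds at 84% | 84 | 1 | 300 | 299 × 5 + 6 = 1,501 |

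The fourth trace is slightly worse than the third, yet its score falls from 300 to 1. At 4 h the steady trace scores 14,400 s. These results follow from the definition alone.

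**How often the timed level is not hypoxaemic.** Background and rationale {6a} gives a sudden drop below 90% in 1.5% of patients on low flow, and 168 per 1,000 in a general procedural sedation population. If the trial's rate lies in that range, 94 × (1 − 0.168) = 78.2 to 94 × (1 − 0.015) = 92.6 of the 94 control patients would be timed at a minimum that is not below 90%.

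**Direction between arms (illustrative).** Simulated 3-h traces, 600 patients per arm: slow wander around a baseline (SD 0.3 or 0.8 points) plus random dips. All of these parameters are assumptions, not figures from the protocol:

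- Fewer dips: mean 3 v 0.8 dips, baseline 97.
- Fewer dips and higher baseline: mean 3 v 0.8 dips, baseline 96.5 v 98.5.
- Shallower dips: mean depth 6 v 2 points, baseline 97.
- Higher baseline only: mean 1 dip in both arms, baseline 95.5 v 98.5.
- Baseline shift, no dips: 95.2 v 98.

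Low flow v high flow, at wander 0.3; 0.8:

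| Scenario | Mean lowest SpO2 (%) | Mean duration (s) | Median duration (s) |
|---|---|---|---|
| Fewer dips | 88.3 v 93.4; 88.2 v 92.4 | 259 v 1,501; 62 v 206 | 22 v 80; 20 v 50 |
| Fewer dips, higher baseline | 88.2 v 94.8; 87.3 v 94.1 | 208 v 1,226; 54 v 209 | 21 v 70; 18 v 53 |
| Shallower dips | 87.1 v 93.7; 86.2 v 93.1 | 178 v 474; 60 v 135 | 17 v 35; 17 v 33 |
| Higher baseline only | 91.0 v 94.5; 90.4 v 93.4 | 1,119 v 1,275; 182 v 187 | 46 v 51; 40 v 38 |
| Baseline shift, no dips | 94.4 v 97.2; 93.1 v 95.9 | 2,988 v 2,759; 330 v 357 | 2,005 v 1,625; 180 v 200 |

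In the first six comparisons (three scenarios, two wander levels) high flow has the higher minimum and the longer duration. The Spearman correlation of lowest SpO2 with its duration is +0.64 to +0.76. The medians reverse as well, so a rank test on the same outcome would not cure it. In those six comparisons the 90%-for-60-s incidence orders the arms correctly (20% to 27% v 1% to 6%), and so does the area below 90%.

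**Case ordered correctly.** Single plateau dips to 85% lasting 180 s and 60 s score 180 and 60.

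**The case against.** **Certainty.** A reader might infer that any real benefit of high flow must appear as harm. The documents do not support that: the reversal needs fewer or shallower dips. A higher baseline with unchanged dips made little difference, a pure baseline shift had no consistent direction, and shorter dips of equal depth were ordered correctly.

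**Planning means.** A reader might also infer from the means of 95.2% and 99.3% in Sample size {14} that high-flow patients will spend longer at their minimum. Those means say nothing about trace shape, which determines the duration, and the section itself warns that they come from a different indication and shorter treatment.

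**Magnitude.** The simulated sizes are not calibrated. In the six reversing comparisons, 20% to 27% of low-flow patients had more than 60 s below 90%, against 1.5% and 16.8% in the protocol for any drop below 90%, and the low-flow mean minimum was 86% to 88% against 95.2% in the sample-size section. The perfectly flat 98% trace is a limiting case. All of this stands, so only the direction is used here, not the size.

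**Reading.** The protocol never says that longer is worse, and the t-test is inferred from a general rule. A reader who sees the lowest value alongside could interpret the seconds better. The authors may also mean the length of the episode containing the nadir. Those points limit the claim but do not remove it: no other analysis is given for a continuous outcome, and an episode reading needs a boundary and a rule for patients without an episode, neither of which is stated.

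**Consequence.** Fixed-threshold outcomes are already in the plan. That stands and limits the severity, although both ignore dips of 60 s or less.

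**Conclusion.** The point holds as a defect of definition. Seconds at a patient-specific minimum are not comparable between patients or arms, and a worse trace can score far fewer seconds (300 s falling to 1 s after one deeper reading). This rests only on the wording in Outcomes {12} and the 3 to 4 h window.

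The claim about direction is weaker. If high flow reduces the number or depth of dips, the outcome can, and probably will, be longer under high flow, which the natural reading takes as worse. That depends on assumed trace shapes and is not a forecast of size for this trial.

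It would go too far to infer that the trial's main conclusion is at risk. The primary outcome, the 90% incidence outcome and the area outcome are all unaffected. One secondary outcome, listed first, cannot be interpreted as written, and it should be changed before the data are analysed.

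**What to change.** Replace the item with cumulative seconds of SpO2 below 90% over the same window and from the same continuous recording, scoring 0 for a patient who never goes below 90%. This has a clear direction and counts the short dips that the two existing threshold outcomes leave out. Add one higher level, fixed before unblinding, because on the protocol's own rates about 78 to 93 of 94 control patients may score zero at 90%. Compare the arms with a rank-based test, since many zeros and a long right tail make a comparison of means unsuitable.

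If the item has to stay, report it descriptively beside each patient's lowest value, with no between-group test.

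Cost: no new data, but a change to a secondary outcome, which the protocol's section on communicating amendments {25} requires to be reported to the Ethical Committee and the trial registry. The 90% measure will carry limited information if desaturation is rare.

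### The device user-friendliness outcome contradicts itself: the sentence on what staff rate asks about difficulty of maintaining oxygenation, which is the preceding outcome

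*Protocol article*

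**What the plan says.** In the protocol article, Outcomes {12}, Secondary outcomes, two ratings by the physician assistant or nurse anaesthetist (PA/NA) follow one another.

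The first is difficulty in maintaining oxygenation status. Its rating instruction is: "The AC will be asked to rate their perceived level of difficulty using a 5-point Likert scale", with five anchors from very difficult to very easy.

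The second is user-friendliness of the device. It opens with "A 5-point Likert scale will be used to rate the PA/NA of user-friendliness of the oxygen delivery device", and its measure method reads "PA/NA rating of user-friendliness of the oxygen delivery device during the procedure using a 5-point Likert" scale. Between these two statements stands the rating instruction: "The AC will rate their perceived level of difficulty of maintaining oxygenation using a 5-point Likert scale", with the same five anchors.

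Under Statistical methods {20a}, Secondary outcomes, the analysis rule is: "The response on the Likert type questions will be analysed separately for each question using the Mann-Whitney" U test. On the Likert ratings by participants and staff, the Discussion adds: "Validated questionnaires were preferred, but unfortunately these are not available".

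**The concern.** An outcome's name, the question put to the rater and the response scale should describe one construct. Here the name and the question describe two. How easy a device is to use and how hard it was to keep the patient oxygenated are different matters, and the protocol treats them as such by listing both.

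At stake is what a result labelled user-friendliness would mean. A form built from the rating instruction would collect oxygenation difficulty a second time, and a named secondary outcome would have no data of its own. The ratings are made soon after each procedure, so a missing item could not be properly recovered later. A form built from the heading or the measure method would collect the right thing, but readers of the published definition could not tell what had been asked.

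**Working it through.** No figure is involved, so the check is a comparison of the two definitions, element by element.

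| Element | Oxygenation difficulty | User-friendliness |
|---|---|---|
| Heading | oxygenation difficulty | user-friendliness of the device |
| Opening sentence | oxygenation difficulty | user-friendliness of the device |
| What the rater scores | perceived difficulty | perceived difficulty of maintaining oxygenation |
| Anchors | five, very difficult to very easy | the same five |
| Low ratings | rater explains the answer | rater explains the answer |
| Timeframe | soon after the procedure ends | the same |
| Measure method | oxygenation difficulty | user-friendliness of the device |

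1. **Internal consistency.** The first column agrees with itself throughout. In the second, three elements name user-friendliness (heading, opening sentence, measure method) and one names oxygenation difficulty (what the rater scores).

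2. **Which element describes the item.** The other three give the label of the outcome. Only the deviating sentence says what the rater is to judge and on which anchors, so someone building the form from this text would turn to it.

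3. **Whether another part of the article repairs it.** None does. The Discussion says that validated questionnaires were not available for these ratings, so no standard instrument is named that would fix the wording.

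4. **Pattern in the other Likert outcomes.** Patient comfort is rated on comfort anchors, and cardiologist satisfaction on satisfaction anchors. Only user-friendliness carries the question of another outcome.

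5. **Consequence for the analysis.** Each Likert question receives its own Mann-Whitney test. If the form follows the deviating sentence, two of these tests address the same question, and one is reported as user-friendliness. If the form asks about the device, the tests address different questions and the analysis is sound.

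One reading is assumed. The rating sentences call the rater AC, which is missing from the abbreviation list. I take this to be the PA/NA group, because the heading and measure method of both outcomes name that group.

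**The case against.** The strongest reply is that this is a slip in the text alone. Three of four descriptive elements are right, including the measure method, which is the field the protocol uses to state how most of its outcomes are measured. The article describes the item in prose and does not reproduce it; the exact wording of a staff question normally sits in the eCRF, which is not shown. Wording carried over from the paragraph above is at least as likely as a duplicated item on the form.

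Much of this stands, and it limits the conclusion. A reader might infer that user-friendliness is simply not measured, that none of the 188 planned participants will have a valid rating, or that the two tests will be almost perfectly correlated. The documents do not support these as facts. The first two hold only if the form copied the deviating sentence, and the correlation was not computed and could not be from this article. Nor does the article claim that the Likert tests are independent of one another, or give any evidence that the two ratings would point in opposite directions for high-flow oxygen.

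It is also fair that sharing anchors is not an error in itself: a scale from very difficult to very easy suits a question about using a device. And the outcome carries modest weight. It is one unvalidated staff rating among more than a dozen secondary outcomes, and the abstract's list of secondary outcomes does not include the staff ratings.

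What the reply does not remove is the contradiction. The article does not leave the question to another document; it states one, and that question belongs to a different outcome.

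**Conclusion.** The point holds as an internal contradiction in the definition of one secondary outcome, one of three rated by staff. It is wrong as written under either reading. If the form follows the rating sentence, a named outcome is lost and a repeat of another is mislabelled. If the form is correct, the published definition misstates what was asked. The documents do not show which applies, so the loss of the outcome is conditional on the form.

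The primary outcome, sample size and power do not depend on this item. The correction is worth making because it is specific and nearly free, and because the Trial status section describes recruitment as started, so ratings may already be accumulating.

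**What to change.** 1. Correct the rating sentence so that staff rate the user-friendliness (ease of use) of the oxygen delivery device. The anchors from very difficult to very easy can be kept if the question is clearly about using the device; a new scale is a matter of preference.
2. Check the eCRF item against the corrected sentence, and change the item if it asks about oxygenation.
3. If ratings have already been collected with the duplicate wording, report them as oxygenation difficulty and not as user-friendliness, and state from which point the corrected question was used.

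The cost is one sentence, one check of the form and, if needed, one changed eCRF item. Under the article's own rule on modifications to outcomes {25}, the change would be communicated to the ethics committee and the registry.
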